### Follow-up

To assess the short-term efficacy and safety of the intervention, participants underwent a 4-week follow-up period immediately after completing treatments. During this period, participantsdid not receive any additional treatment, and there was no direct researcher supervision. At the end of the 16-week period, participants were required to complete a third test. Furthermore, participants had the opportunity to communicate their clinical symptoms and report any adverse events through in-person discussions, text messages, or via online communication platforms at the designated time points.

### Data collecting and monitoring

Demographic and baseline characteristic data were gathered by outcome assessors at the time of participant recruitment. In order to maintain data accuracy, two independent data administrators performed data entry and conducted thorough proofreading. Once the data integrity was verified, the database was reviewed and confirmed by a qualified expert and two principal research members. Subsequently, the database was locked, with access restricted to the data administrators and the statistician.

### Statistical analyses

Demographic and baseline information will be compared among the different groups. The Kolmogorov-Smirnov test will be employed to assess the normality of data. For intragroup hypothesis testing, differences across various time points will be evaluated using repeated measures analysis of variance (RM-ANOVA) for normally distributed data, and Friedman’s test will be employed for data not following a normal distribution. In the case of intergroup hypothesis testing, normally distributed data will be analyzed using multivariate analysis of variance (ANOVA), while non-normally distributed data will be analyzed using the Kruskal-Wallis H test. Generalized Estimating Equation (GEE) model will be used to assess how the primary outcome measures, SC-NPAD, change over time across the three intervention groups. Covariates such as demographic factors, and other relevant variables will be included in the model to account for potential confounding effects. The GEE model will also be employed to examine the effects of the intervention on secondary outcome measures, such as SNPA scores for neck and shoulder posture and function, SF-36 scores for quality of life, and levels of neurotransmitters (5-HT, NE/NA, GABA, ACTH, β-EP, and CGRP) obtained from blood tests. Similar to the primary outcome analysis, this analysis will consider the longitudinal nature of the data and adjust for potential confounders. The GEE model will estimate the average change in outcome measures over time within each intervention group and to compare the differences in changes between the intervention groups and the control group. Interaction terms may be included in the model to examine whether the effects of the intervention vary over time or across different groups of participants. Appropriate adjustments for multiple comparisons will be made if necessary. Statistical significance will be taken at 2-sided *P* < 0.05. Statistical analyses will be performed using SAS 9.4 (SAS Institute Inc., Cary, NC).

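### The plan names GEE for SC-NPAD but fixes no deciding contrast, visit or interaction test and makes multiplicity adjustment conditional, so the 5% level is not secured

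*Protocol article*

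**What the plan says.** All of this stands in the Protocol article, Statistical analyses, unless another section is named.

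- **Pre-test.** "The Kolmogorov-Smirnov test will be employed to assess the normality of data".
- **Within-arm tests.** "differences across various time points will be evaluated using repeated measures analysis of variance (RM-ANOVA) for normally distributed data", with Friedman's test otherwise.
- **Between-arm tests.** "normally distributed data will be analyzed using multivariate analysis of variance (ANOVA), while non-normally distributed data will be analyzed using the Kruskal-Wallis H test".
- **GEE.** A GEE model is assigned to SC-NPAD by name, and the text then refers back to it as the analysis of the primary outcome. It compares the change in each active group with the change in the control group. Interaction terms are permitted, not required.
- **Error control.** "Appropriate adjustments for multiple comparisons will be made if necessary". "Statistical significance will be taken at 2-sided *P* < 0.05".
- **Visits.** The Interventions section sets assessments at baseline, week 12 and week 16. No section says which post-baseline visit decides.
- **Abstract, Methods.** Repeated measures ANOVA and GEE are listed side by side for the outcomes.
- **Sample size.** The trial is sized on an ANOVA F test with the full 0.05 spent once.

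**The concern.** GEE is the named analysis, but naming a model does not name a test. The model as described yields two active-versus-control contrasts at each of two visits, and the plan does not say which one carries the efficacy claim. The group-by-visit term is what expresses a difference in change between arms, so leaving it optional leaves the treatment test itself optional. A conditional adjustment with no method, family or trigger does not close the gap.

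The within-arm and ANOVA or Kruskal-Wallis sentences exempt no outcome, so they also produce p-values for SC-NPAD at 0.05. The pre-test lets the data choose between a comparison of means and a comparison of ranks with about 20 people per arm. The between-arm sentence attaches the name of one method, multivariate analysis of variance, to the abbreviation of another.

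At stake is whether a p-value below 0.05 on SC-NPAD can be read at face value. If the contrast and visit are settled after the results are seen, it cannot.

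**Working it through.** **Inputs.** From the documents: two-sided alpha 0.05; three equal arms of 20 (60 recruited); visits at baseline, week 12 and week 16; GEE contrasts DT versus control and M+FE versus control. Assumed, because none is stated: the correlation between visits (0.3, 0.5 or 0.7, equal for all pairs), normal data and no dropout.

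**1. The plan's own figure.** Noncentral F with λ = f² × N. For f = 0.4 and N = 52, λ = 0.16 × 52 = 8.32. With 1 numerator df (two groups) the power is 0.807, and 52 is the smallest N reaching 0.80. Attrition: 52 / 0.90 = 57.8, so 58, rounded up to 60. The three-group one-way F test (2 df) would need 64, or 66 if balanced. That mismatch is a separate matter. What counts here is that the calculation spends 0.05 on one test and reserves nothing for several.

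**2. Rough guide.** With k independent tests at 0.05 the chance of at least one false positive is 1 − 0.95^k. For k = 2 it is 1 − 0.9025 = 9.75%. For k = 4 it is 1 − 0.8145 = 18.5%. The planned tests are correlated, so simulation is needed.

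**3. Simulation under no treatment effect** (20 per arm, 20,000 runs per correlation, no adjustment; contrasts are t tests on change from baseline unless stated):

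| What may count as success on SC-NPAD | ρ = 0.3 | ρ = 0.5 | ρ = 0.7 |
|---|---|---|---|
| DT vs control, week 12 only | 5.1% | 5.1% | 4.7% |
| DT vs control, week 12 or 16 | 9.3% | 9.2% | 8.9% |
| Both active-vs-control contrasts, both visits | 16.7% | 16.1% | 15.7% |
| Those four, or ANOVA at either visit | 22.5% | 22.6% | 22.3% |
| Both contrasts, both visits, uncorrected robust GEE Wald | 20.3% | 20.1% | 19.7% |

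The last two rows need a note. The ANOVA row takes ANOVA on the raw scores at each visit. The plan does not say whether raw scores or changes are meant; re-running the same set-up with ANOVA on changes gives about 17.5-18%. The robust Wald row is higher because the uncorrected sandwich variance is itself liberal at 20 per arm: 6.2-6.5% for a single contrast.

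**4. The normality gate alone.** Kolmogorov-Smirnov with estimated parameters in each arm, then ANOVA if all arms pass and Kruskal-Wallis otherwise (5,000 runs): 5.1% on normal data and 5.4% on lognormal data. The gate is not the source of the inflation.

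**5. Within-arm tests.** If every arm improves by 0.5 SD with no treatment effect (ρ = 0.5), a paired test in one arm of 20 is significant about 56% of the time. Such a test says nothing about treatment.

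**The case against.** Several stronger readings are tempting, and the text does not support them.

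- **That no analysis of SC-NPAD is named as primary.** GEE is assigned to it by name and later called the analysis of the primary outcome, while the other test sentences name no outcome. What remains open is the contrast, the visit and the interaction test.
- **That the 5% rate fails outright.** The plan does foresee adjustment, and an analysis plan not shown may define it. If one is applied, 5% can be held. The supportable statement is that the protocol does not guarantee it.
- **That the Kolmogorov-Smirnov gate inflates the error.** Step 4 shows that it hardly does.
- **That the error is 21-28%.** Those figures come from all six pairwise contrasts (three pairs at two visits), without and with two ANOVAs. The GEE sentence plans only comparisons with control. The wider aim in the Abstract, DT against other interventions, does not amount to a planned DT versus M+FE test.
- **That significance within the DT arm will be presented as efficacy.** Under assumed inputs (18 per arm, common change of 0.4-0.5 SD, correlation 0.6) DT would be significant and control not about 24% of the time. But the plan labels these tests as intragroup, keeps them apart from intergroup testing, and nowhere counts them as evidence of efficacy.
- **That the ANOVA and Kruskal-Wallis tests ignore baseline.** The plan does not say whether they use raw scores or changes.

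It is also fair that the Abstract foresees a larger trial if feasibility is shown, which lowers the confirmatory stakes. These points narrow the criticism without removing it. The optional interaction, the conditional adjustment and the parallel tests at 0.05 are stated rules, not details an article merely left out.

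**Conclusion.** The point holds in a limited form and should be fixed. GEE is the stated primary analysis, but the plan does not say which of its results decides, and it ties adjustment to an undefined condition. If nothing is adjusted, the false-positive chance on SC-NPAD is about 9% when DT versus control may succeed at either visit. It is about 16% when both planned contrasts at both visits count, and 22-23% when raw-score ANOVAs at both visits count as well. These figures assume 20 per arm, normal data and a correlation of 0.5 to 0.7; a correlation of 0.3 changes them little. Which figure applies depends on what the investigators would accept as success, and the document does not say. Two lesser faults stand apart from the inflation: the data-driven choice between tests of different hypotheses, and the ambiguous name for the between-arm method.

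**What to change.** Replace the conditional adjustment sentence, and record the following before treatment codes are revealed:

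1. One longitudinal model of SC-NPAD is the sole confirmatory analysis: GEE with a small-sample variance correction, or a mixed model. It includes a mandatory group-by-visit term and adjusts for baseline SC-NPAD.
2. One visit is named as primary. Week 12, the end of the intervention, is an example; the choice is the investigators'.
3. The DT contrasts that carry the claim are named, and Holm or a fixed order is applied over them. If DT versus M+FE matters to the aim, it must be in that list.
4. The normality gate is dropped. A rank-based or bootstrap analysis of the same contrast serves as the sensitivity analysis.
5. Within-arm changes are reported as means with confidence intervals, without tests.
6. If a between-arm ANOVA is kept as supportive, one method is named, with the scores it uses.

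With one pre-named contrast at one visit and a t reference, the simulated error is 4.7-5.1%.

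**Cost.** Wording and fewer p-values, plus some power if Holm is chosen. For a pairwise difference of d = 0.8 (assumed; f = 0.4 with two groups gives d = 2f), the normal approximation at 20 per arm gives Φ(0.8 × √10 − 1.960) = Φ(0.570) = 0.72 at 0.05. At 0.025 it is Φ(2.530 − 2.241) = 0.61. Holm over two contrasts lies between these, so the loss per contrast is at most about 10 percentage points. A fixed order costs the first contrast nothing.

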### Sample size

The sample size for this study was calculated using the G*Power software (version 3.1.9.7, University of Düsseldorf, Germany). The calculation was based on recent controlled trial studies related to exercise interventions for neck pain [26].Specifically, we employed the F test within the ANOVA framework with an effect size (Cohen’s f) set at 0.4, a significance level (α) of 0.05, and a desired statistical power (1 - β) of 0.8. The calculations determined that a minimum total sample size of 52 individuals was necessary for this study. To accommodate a potential 10% attrition rate, our recruitment target was set at 60 participants, evenly distributed across three groups, with a minimum of 20 participants per group. 

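### GEE with about 18–20 participants per arm and no small-sample method: in its usual robust form each change contrast runs at about 6.4–6.5% instead of 5%, and a joint group-by-time Wald test, if used, at about 9.5–10%

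*Protocol article*

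**What the plan says.** The Statistical analyses section of the protocol article makes GEE the longitudinal model for the primary outcome: "Generalized Estimating Equation (GEE) model will be used to assess how the primary outcome measures, SC-NPAD, change over time across the three intervention groups". It extends the model to posture and range of motion, quality of life and the blood markers. The model is to estimate the change within each group and to compare the changes in the two intervention groups with the change in the control group. Interaction terms are optional. On adjustment the section says: "Covariates such as demographic factors, and other relevant variables will be included in the model". On the level it says: "Statistical significance will be taken at 2-sided" P < 0.05. The software is SAS 9.4. The section names no variance estimator, test statistic, reference distribution, working correlation or small-sample correction.

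On size, the Sample size section says "our recruitment target was set at 60 participants, evenly distributed across three groups", which is 20 per arm. It also says "To accommodate a potential 10% attrition rate", which leaves about 18 per arm. The Interventions section gives three assessments: baseline, week 12 and week 16.

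**The concern.** The usual GEE inference, an empirical sandwich variance referred to a normal or chi-square distribution, is justified as the number of independent participants becomes large. With about 20 per arm, two things go wrong in the same direction. The sandwich is built from residuals that have already been fitted, so it is too small on average. The normal or chi-square cut-off also ignores the uncertainty in that variance. Both make p-values too small and intervals too narrow. The effect arises with complete, balanced, normal data, so it is separate from dropout and from non-normality.

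At stake is whether the stated two-sided 5% level is delivered for the primary outcome and for each secondary outcome analysed in the same way. The open-ended covariate list can add to the problem, because each fitted parameter shrinks the residuals further.

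**Working it through.** **The plan's own figures.** The figure under test is the nominal 5% level, which is a threshold and cannot be reproduced. The only computed figure nearby is in the Sample size section: "a minimum total sample size of 52 individuals was necessary for this study", with "effect size (Cohen’s f) set at 0.4" and "a significance level (α) of 0.05, and a desired statistical power (1 - β) of 0.8". From the noncentral F with noncentrality N·f², 52 is the minimum for a two-group one-way ANOVA (power 0.807). For three groups the minimum is 64, or 66 if balanced. That is a separate matter. The check below uses only the arm size.

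**Inputs.** From the article: three arms, 20 per arm (18 after 10% attrition: 20 × 0.9), three assessments, two-sided 5%. Assumed, because the article gives neither: normal outcomes, and a within-person correlation of 0.3 to 0.7 (exchangeable) or 0.6 (first-order autoregressive).

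**Step 1: one contrast of change against control (1 df), exact.** With a saturated group-by-time model and complete data, the sandwich variance of the contrast is (n−1)/n times the unbiased one. The type I error is therefore

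P(|t with 2n−2 df| > 1.96 × √((n−1)/n)).

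- n = 20: 1.96 × √(19/20) = 1.910; on 38 df this gives 6.4%.
- n = 18: 1.96 × √(17/18) = 1.905; on 34 df this gives 6.5%.

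Simulation (40,000 runs, exchangeable correlation) agrees: 6.3–6.4% at 20 per arm and 6.6% at 18.

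The interval width relative to a correct t interval is 1.910/2.024 = 0.94 at n = 20 and 1.905/2.032 = 0.94 at n = 18, so the intervals are about 6% too narrow.

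**Step 2: joint test of group by time.** Three groups and three times give (3−1) × (3−1) = 4 df. The null was simulated, with each version tested against the 5% point of chi-square on 4 df:

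| Version of the 4-df test | 20 per arm | 18 per arm |
|---|---|---|
| Robust Wald, uncorrected, exchangeable data | 9.4–9.5% | 10.0–10.1% |
| Generalized score | 4.3–4.5% | 4.3% |
| Model-based Wald, exchangeable working correlation, no covariates | 5.6% | not run |
| Model-based Wald, exchangeable, three covariates | 5.4% (with 10% dropout) | 5.2% |
| Model-based Wald, pooled unstructured covariance | 7.7–8.0% | 8.1–8.2% |

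The exchangeable model-based rows use 4,000 runs, with data generated under that same correlation; the other rows use 40,000. With autoregressive data at 20 per arm, the robust Wald test gives 9.6%. With lognormal data it gives 8.8%. At 60 per arm it falls to 6.2%, which confirms that this is a small-sample effect.

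**Step 3: covariates.** With three covariates and 10% dropout at 20 per arm (4,000 runs), the robust Wald test gives 9.7% on 4 df and 6.5% on 1 df, hardly different from Steps 1 and 2. With baseline plus five covariates (6,000 runs; the number is an assumption), the 1-df contrast gives 7.3% at 20 per arm and 7.6% at 18, and the joint test gives 11.6% and 12.5%.

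**Step 4: after correction.** The 1-df contrast with a corrected variance and a t reference gives 4.9–5.1%. The 4-df test with a Mancl-DeRouen type variance and an F reference gives 5.6–5.7%.

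**The case against.** The strongest reply is that the article specifies none of the procedure that produces these errors. It names no Wald test, no sandwich and no chi-square cut-off, and it does not exclude a correction. These details are commonly left to the statistical analysis plan, and this is a condensed article. All of that stands, so the silence is not in itself an error.

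A reader might infer that the plan's main test rejects a true null 10% of the time. The text does not support this. It calls no group-by-time test the main one and makes interaction terms optional. The comparison it does name is between each intervention group and control, a 1-df contrast whose error is about 6.4–6.5% even in uncorrected form. The 10% belongs to one version of a joint test, while a score test of the same hypothesis is slightly conservative.

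A reader might also infer that covariate adjustment necessarily makes matters much worse. That depends on how many are used: three made almost no difference, and the larger figures rest on an assumed six.

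What the reply does not remove is that GEE, the arm size and the 5% level are all fixed in the article, and that GEE in its usual robust form is anti-conservative at this size. The model-based route is not a general escape either. It came near 5% with a correctly chosen exchangeable structure, but near 8% with an unstructured one and no degrees-of-freedom correction.

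**Conclusion.** The point holds in conditional form, as a cheap improvement and not as an error in the article. If the uncorrected sandwich is used with a normal or chi-square reference, each named contrast of change runs at about 6.4–6.5% instead of 5%, and a joint 4-df Wald test, if used, at about 9.5–10%. Across the tests of the joint hypothesis that the text leaves open, the true level ranges from about 4% to 10%.

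The contrast figure is exact for complete normal data with equal covariance across arms. The joint figure comes from simulation and changes little over the correlations tried. How many covariates will be fitted is not known, so any further inflation from them cannot be fixed.

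**What to change.** In the Statistical analyses section, or in the statistical analysis plan if it is silent too, keep GEE and name a small-sample-corrected sandwich, such as Mancl-DeRouen or Morel-Bokossa-Neerchal, with a t or F reference. A mixed model for repeated measures with unstructured covariance and Kenward-Roger degrees of freedom would serve the same purpose. State that the inference rests on the contrasts of each intervention group with control, and whether a joint group-by-time test will be reported. Limit covariates to the baseline value and one or two others, named before the data are seen.

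The cost is a sentence or two of wording and a change to the analysis program. No data collection changes. Intervals become slightly wider: for a single contrast, by a factor of about 2.024/1.910 = 1.06 at 20 per arm.

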**Methods:**

A 12-week RCT was conducted, with participants undergoing randomization into one of three groups: DT, Meditation + Fitness Exercise (M+FE), or a control group. Participants in the DT and M + FE groups attended their respective training classes three times per week for 12 weeks. Participants in the control group were required to attend health education workshops every 2 weeks. Following the 12-week intervention period, all participants underwent follow-up assessments at the 16th week. Outcome measures encompassed the Simplified Chinese Neck Pain and Disability Scale (SC-NPAD) and Visual Analog Scale (VAS) for pain assessment, Static Neck Posture Assessment (SNPA) to evaluate neck and shoulder posture and function, Short Form-36 (SF-36) to assess quality of life, and blood tests measuring 5-Hydroxytryptamine (5-HT), Norepinephrine/Noradrenaline (NE/NA), γ-aminobutyric acid (GABA), Adreno-Cortico-Tropic-Hormone (ACTH), β-Endorphin (β-EP), and Calcitonin-Gene-Related Peptide (CGRP) levels via high-performance liquid chromatography (HPLC), chemiluminescence immunoassay (CLIA), enzyme-linked immunosorbent assay (ELISA), and radioimmunoassay (RIA). Brain activity changes were monitored through MRI scans. Repeated measures analyses of variance (ANOVAs) will be used to evaluate the outcomes at baseline, at the 12th week, and at the 16th week. Generalized Estimating Equation (GEE) models will be applied to analyze changes in outcomes over time and differences between groups.

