### Interventions

Participants in the DT and M + FE groups attended their respective training classes three times a week for 12 weeks. Coaches instructed and corrected movements during these sessions, teaching Daoyin, meditation, and fitness exercises. Instructional videos were provided to participants for home practice, and participants could send self-recorded videos to coaches via online communication platforms for feedback. Each DT or M + FE exercise classlasted 40 min continuously, excluding warm-up and relaxation time. Assessments were conducted at baseline, at the conclusion of the 12-week intervention period, and again at the 16-week.

Within each class of the DT group, participants underwent Daoyin exercise tailored for neck pain following a 3-step protocol. This protocol included a 10-min warm-up exercise session involving joint and basic Daoyin exercise to prevent sports injuries. The subsequent 40-min Daoyin exercise session comprised guided single, combination, and full-body movements. Finally, a 10-min relaxation exercise sessionfollowed to soothe and relax the body.

Within each class of the M + FE group, participants received a combination of meditation and fitness exercises designed to address neck pain, following a similar 3-step protocol. The warm-up sessionlasted for 10 min and involved joint exercises and basic limb movements. This was followed by a 40-min session consisting of 20 min of guided meditation activities and 20 min of single, combined, and comprehensive fitness exercises focused on neck pain. Lastly, participants engaged in a 10-min relaxation exercise session.

The control group did not receive any specific intervention but were instructed to continue their daily routines. However, participants in the control group were required to attend health education workshops every 2 weeks as part of their study participation.

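### The primary GEE is meant to compare changes between arms, but the group-by-time terms that deliver this comparison when baseline is a repeated response are left optional

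*Protocol article*

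**What the plan says.** In the protocol article, Statistical analyses, the GEE is the model for the primary outcome. It is to assess how SC-NPAD scores "change over time across the three intervention groups". Between arms, its task is to "compare the differences in changes between the intervention groups and the control group"; inside each arm, its task is to "estimate the average change in outcome measures over time within each intervention group". All three are stated as firm intentions.

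The next sentence is permissive: "Interaction terms may be included in the model to examine whether the effects of the intervention vary over time". It goes on to mention variation across groups of participants as well.

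There are three measurement occasions. Under Interventions: "Assessments were conducted at baseline, at the conclusion of the 12-week intervention period, and again at the 16-week". The Methods paragraph of the Abstract lists the same three for the repeated-measures ANOVAs, which are to "evaluate the outcomes at baseline, at the 12th week, and at the 16th week", and then assigns the GEE to change over time and group differences. Adjustment is for demographic factors and unspecified other variables; baseline SC-NPAD is not named. The article does not state the working correlation, how time is coded, or whether baseline enters the GEE as response or covariate.

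**The concern.** With baseline among the responses, a model containing only group and visit forces the same change on every arm. It has no parameter for a difference in changes. Its group coefficient mixes the pre-treatment difference, which is zero in expectation under randomisation, with the two post-treatment differences. The section therefore promises one contrast and permits a model that cannot produce it.

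Two things are at stake. The primary result could be reported from a coefficient that is not the treatment effect and is pulled toward zero. And because the term is discretionary, the choice between two different target quantities could be made after the data are seen.

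**Working it through.** The article gives no figure for this effect, so there is nothing of its own to reproduce. Its minimum sample size of 52 is a separate matter and is not used here.

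**Inputs.**
- From the article: three visits (baseline, weeks 12 and 16); two-sided 5% level; 60 recruited in three equal arms; 10% attrition. This gives 60 × 0.9 / 3 = 18 completers per arm.
- Assumed, because the article does not state them: a true effect of d = 0.8 SD at both post-baseline visits (the two-group equivalent of the planning value f = 0.4, since d = 2f); equal variances; complete data; within-person correlation ρ of 0.3, 0.5 or 0.7.

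**Step 1: what the group-plus-visit model estimates.** With true differences (0, d₁₂, d₁₆) and independence or exchangeable correlation, the group coefficient is the plain average over visits, (0 + d₁₂ + d₁₆)/3. For d₁₂ = d₁₆ = d this is 2d/3 = 0.667d, so d = 0.8 becomes 0.53. A check with 300 simulated GEE fits (20 per arm, ρ = 0.5, true effect 1.0) gave a mean of 0.652 (simulation SE 0.016) without the interaction. The week-12 group-by-visit term averaged 0.997.

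**Step 2: how far one third depends on assumptions.** Fraction of the week-12 effect retained by the group coefficient, from generalised least squares:

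| Correlation structure | Equal effect at weeks 12 and 16 | Halved by week 16 | Gone by week 16 |
|---|---|---|---|
| Independence or exchangeable | 0.67 | 0.50 | 0.33 |
| AR(1), ρ from 0.3 to 0.8 | 0.63 to 0.55 | 0.44 to 0.32 | 0.26 to 0.09 |
| Unstructured (0.4, 0.4, 0.8)* | 0.55 | 0.41 | 0.27 |
| Unstructured (0.5, 0.3, 0.7)* | 0.54 | 0.33 | 0.12 |

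*Correlations for baseline–week 12, baseline–week 16 and week 12–week 16.

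For a constant effect the loss is thus 33% to 46%. If the effect halves or vanishes by week 16, the loss is 50% to 67% of the week-12 effect under exchangeable correlation, and more under the others.

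**Step 3: power for Daoyin versus control**, n = 18 per arm, exchangeable correlation. Standard errors in SD units:
- group-plus-visit: √[(2/n)(1 + 2ρ)/3], for an expected estimate of 0.53;
- unadjusted week-12 change: √[(2/n) · 2(1 − ρ)], for 0.80;
- baseline-adjusted week 12: √[(2/n)(1 − ρ²)], for 0.80.

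At ρ = 0.5 these are 0.272, 0.333 and 0.289, so the ratios of estimate to standard error are 1.96, 2.40 and 2.77. Power from the noncentral t distribution (34 df; 33 for the adjusted contrast):

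| ρ | Group-plus-visit, no interaction | Unadjusted week-12 change | Baseline-adjusted week 12 |
|---|---|---|---|
| 0.3 | 0.57 | 0.50 | 0.69 |
| 0.5 | 0.48 | 0.65 | 0.77 |
| 0.7 | 0.41 | 0.85 | 0.90 |

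The first two columns cross near ρ = 0.36. At ρ = 0.2 the three figures are 0.62, 0.45 and 0.66. The baseline-adjusted contrast is ahead at every correlation computed.

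**The case against.** A reader might infer that the trial has chosen a main-effects model and will report a diluted effect. The article does not support that. The sentence just before the permissive one commits firmly to the right contrast, and a group-plus-visit model with baseline as a response would breach that commitment.

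Nor does the article say outright that baseline is a response in the GEE; the explicit list of three visits is attached to the repeated-measures ANOVAs. If the GEE were fitted to change scores, or to weeks 12 and 16 with baseline as covariate, the group term would already be a treatment effect. An optional group-by-visit term would then only ask whether that effect differs between the two visits, and nothing would be diluted. Exact model terms are also commonly left to a statistical analysis plan, which is not shown here.

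Two further stronger readings fail. One third is not a fixed figure, since it needs an equal effect at both visits and a particular correlation structure. And loss of power is not universal: below a correlation of about 0.36 the no-interaction model has more power than a plain change contrast.

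All of this limits the point without removing it. Change scores are not mentioned and baseline SC-NPAD is not a named covariate, so baseline as a response remains the natural reading of a model for change over time. The difficulty is also more than silence: the article itself makes discretionary a term that, on that reading, its own stated comparison requires.

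**Conclusion.** The concern holds as an internal inconsistency in Statistical analyses, conditional on baseline being a repeated response. On that condition, omitting group-by-time gives a coefficient that is not the stated contrast. It is one third too small in the simplest case, and the loss was larger in the other structures tried or when the effect fades by week 16. At the assumed 0.8 SD and 18 per arm, the baseline-adjusted week-12 contrast has 0.12, 0.29 and 0.49 more power than the no-interaction model at ρ = 0.3, 0.5 and 0.7. The effect size, correlations and complete data are illustrative assumptions, not figures from the article. Correcting the wording is a free improvement and should be made.

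**What to change.** State that the primary GEE takes SC-NPAD at weeks 12 and 16 as the outcomes, with baseline SC-NPAD as a covariate, and includes group, categorical visit and group-by-visit. Define the treatment effect as the between-group difference at one named post-baseline visit. An equivalent option keeps all three visits as responses with the baseline means constrained equal across arms. Reserve the permissive wording for interactions with participant subgroups.

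The cost is one or two sentences and no new data, since baseline SC-NPAD is already collected. In the covariate form the model gains one baseline slope and one group-by-visit term per active arm. Merely making the interaction compulsory with unadjusted change would restore the stated contrast, but would not improve power at low correlation; the baseline adjustment does that. The wording should be settled before group labels are revealed to the statistician.
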